#### Parental uncertainty

Parental uncertainty is understood as the degree of certainty/uncertainty the parents have in relation to their children being transferred to adult care. This outcome is measured through LAS with the end points ‘extremely uncertain’ (=100) and ‘not uncertain at all’ (=0). This LAS has been developed for the purpose of the present study.

In addition to the primary and secondary end points, we will calculate a composite end point. We will do so because the transition programme is a complex intervention that may have varying effects on different outcomes. Prior studies on the impact of transition programmes showed that the intervention has impacted on transition readiness,^16^ patient knowledge,^16^ quality of life^42^ and psychosocial health.^42^ Therefore, each patient will be categorised as improved or not. Patients will be classified as improved if they have an improvement in empowerment, transition readiness, knowledge, quality of life or psychosocial health of 0.5 SDs compared with their baseline measurement.

### Data management

Data are entered into a web-based system by the TC and the DCO. Those with access to the system are the TC, DCO, project coordinator and principal investigator, each of whom has a personal login. All data are checked for completeness and the quality of the data is monitored at least twice a year by the members of the research group. This process is carried out by verifying records with the raw data and checking frequency distributions to identify responses outside of the given possibilities.

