### Intervention

#### Transition programme (intervention group)

This study implements a multicomponent intervention, adapted from a brief transition programme developed by Hilderson *et al*.^23^ Adaptation of the programme followed the intervention mapping process.^24^ Intervention mapping is a thorough method used to build comprehensive programmes for health promotion and consists of six consecutive steps: (1) assessment of the needs of the target population; (2) defining programme objectives by specifying performance and change objectives; (3) determining theory-based intervention methods and practical strategies; (4) designing and producing the intervention programme; (5) adoption and implementation of the intervention; and (6) developing and executing a plan for evaluation.^24^ Applying the intervention mapping method in this study ensures that the intervention is well-grounded and includes the necessary components to target the programme objectives. A detailed description of each of the steps will be given in a related article.

The transition programme includes eight key components: (1) a TC; (2) a written person-centred transition plan; (3) provision of information and education about the condition, treatment and health behaviours; (4) availability by telephone and email; (5) information about and contact with the Grown-Up Congenital Heart Disease (GUCH) clinic; (6) guidance of parents; (7) meeting with peers; and (8) the actual transfer to the GUCH clinic.

These components are implemented in five steps: (1) a first patient visit with the TC; (2) a second outpatient visit with the TC; (3) information day for adolescents and their parents; (4) a third outpatient visit with the TC; and (5) actual transfer to the GUCH clinic. The TCs are specialised nurses at the outpatient clinic of paediatric cardiology who have received specific training in performing this intervention.

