### Blinding

Owing to the nature of the intervention and the study design, it is not possible to blind the participants, TCs or DCOs. However, the TCs and DCOs in charge of carrying out the intervention and data collection are not involved in the preparation of the intervention design or in the statistical analyses.

To avoid cross-contamination between the comparison and the intervention group within the RCT centres, TCs are not involved in the delivery of care of the comparison group and other healthcare professionals in the participating centres will not be informed of the intervention components. DCOs in the control group do not participate in discussions of the intervention.

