#### Knowledge about CHD

Adolescents' knowledge about their CHD is assessed with the Knowledge Scale for adults with Congenital Malformed Hearts (KnoCoMH).^28^ This instrument evaluates the level of knowledge within four domains: disease and its treatment; complications prevention; physical activity; and reproductive issues.^28^ The questionnaire includes 19 items and scores are calculated by dichotomising answers as correct or incorrect. Access to the medical files is needed in order to confirm the answers in some of the items. For participants for whom medical treatment or endocarditis prophylaxis is not recommended, the domains are excluded.

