Irrespective of these strengths, we anticipate some limitations as well. First, we are not able to blind the participants or the healthcare team that will perform the intervention. To minimise a potential impact, neither the therapeutic team nor the TCs participate in the data analysis. Second, there is a possibility of a relatively long period of recruitment for participants which can require extending the trial period and delaying data analysis. Third, transition interventions have been advised to start early on, for example, between 10 and 12 years of age, and have a long follow-up.^51^ Furthermore, a long follow-up allows continuity of care to be measured in this population and provides insight into the effects of the transition programme over this parameter. Although we recognise the importance of starting early, it would have jeopardised the feasibility of the study, because it would have taken almost a decade to finish recruitment and follow-up until the age of 18 years. Nonetheless, it could be possible to later on assess loss of follow-up in a separate study.

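### Transition coordinators who deliver the programme may also enter and see outcome data, with no stated limit by arm or data type: an avoidable bias route, clearest for the knowledge scale

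*Protocol article*

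**What the plan says.** The Data management section of the protocol article assigns entry to two roles: "Data are entered into a web-based system by the TC and the DCO". It then lists who can get in: "Those with access to the system are the TC, DCO, project coordinator and principal investigator, each of whom has a personal login". It separates neither arms nor types of data, so outcome questionnaires and process forms are not distinguished. The same section has the research group check entered records against the raw data at least twice a year.

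The TC is the person who delivers the intervention. Under Transition programme (intervention group): "The TCs are specialised nurses at the outpatient clinic of paediatric cardiology who have received specific training in performing this intervention". The three programme visits are held with the TC.

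The Blinding section concedes that "it is not possible to blind the participants, TCs or DCOs", and offers as mitigation that both roles "are not involved in the preparation of the intervention design or in the statistical analyses". The limitations in the Discussion repeat the analysis half of this: "To minimise a potential impact, neither the therapeutic team nor the TCs participate in the data analysis".

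For the knowledge scale (KnoCoMH), answers are scored as correct or incorrect, and "Access to the medical files is needed in order to confirm the answers in some of the items". No scorer is named. Knowledge is one of the five measures in the composite end point defined at the end of the Parental uncertainty section.

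**The concern.** In an open trial with patient-reported outcomes, an unblinded therapist can influence the data while forms are collected, read and scored. Keeping that person out of the analysis comes too late in the chain to prevent this. As written, the plan closes the analysis step and leaves the earlier steps open.

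Two exposures follow:

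- **Scoring.** Confirming a knowledge answer against the file is a staff judgement. If the TC makes it, the person who taught the content decides whether the answer is right, knowing the arm. The effect would carry into the composite, where a gain of 0.5 SD on any one of five measures classes the patient as improved.
- **Answering.** Intervention patients may complete questionnaires about empowerment, alcohol and tobacco knowing that the nurse they work with can handle or read them. Comparison patients have no programme relationship with a TC.

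At stake is whether a difference between the randomised arms on these outcomes can be credited to the programme and not partly to the handling of the forms.

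**Working it through.** The point concerns who handles the data, so the main check is to set the sections side by side.

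1. **Delivers the programme:** the TC (Transition programme section).
2. **Knows the allocation:** the TC, who also operates the randomisation system (Randomisation and Blinding sections).
3. **Enters data and holds a login:** the TC, together with the DCO (Data management). No limit by arm or data type is stated.
4. **Collects data:** the Blinding section speaks of "the TCs and DCOs in charge of carrying out the intervention and data collection are not involved in the preparation of the intervention design". This can mean that both roles do both tasks, or that TCs treat and DCOs collect.
5. **Scores knowledge:** not stated (Knowledge about CHD). Some of the 19 items need the file. Domains are also dropped for patients for whom medical treatment or endocarditis prophylaxis is not recommended, which is a further step at which someone must decide.
6. **Scores GYPES:** no judgement is needed. It is the sum of 15 Likert items answered by the patient (Primary outcome measures).
7. **Kept out by the safeguard:** TCs and DCOs, from intervention design and statistical analysis only.

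Items 1 to 3 establish that the programme's deliverer can enter and view data. Item 7 shows that the safeguard does not reach that step. Items 5 and 6 show where judgement could enter: some knowledge items, and through them the composite, but not the arithmetic of the primary score.

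**The plan's own figures.** The target is 5.25 points = 0.5 SD, so SD = 5.25 / 0.5 = 10.5.

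- n per arm = 2 × (1.960 + 0.842)² × (10.5 / 5.25)² = 62.8, rounded up to 63.
- With 10% dropout: 63 / 0.9 = 70.

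Both agree with the Sample size estimation section, and this point changes neither.

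**Purely illustrative sensitivity.** The article gives no size for any bias from form handling. To show only how the primary test responds to a spurious shift, whatever its source:

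- SE of the difference = 10.5 × √(2/63) = 1.87.
- No shift: rejection probability 5%, the nominal level.
- Assumed shift of 1 point: z = 1 / 1.87 = 0.53, rejection probability 0.077 + 0.006 = 0.083.
- Assumed shift of 2 points: z = 2 / 1.87 = 1.07, rejection probability 0.187 + 0.001 = 0.188.

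Nothing in the article supports 1 or 2 points over zero, so these figures are not an estimate of the harm done by this arrangement.

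**The case against.** The strongest reply is that the division of work is inferred. TCs fill in three process forms of their own (Intervention fidelity section), so they would need a login even if DCOs handled every outcome questionnaire. The standard operating procedures are said to cover survey completion and data entry and security, and they may well restrict access. No section gives knowledge scoring to the TC. These observations stand: they limit the point to what Data management permits and do not show what happens in practice. They do not remove it, because that section grants entry and access in positive terms and without restriction. If a procedure says otherwise, the two should be reconciled.

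A second reply is that the primary score needs no staff judgement and records are verified against raw data. This also stands for entry errors. Verification cannot detect an answer shaded because of who might read it, and no blinded re-scoring of knowledge items is described.

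A third reply is that participants cannot be blinded, so some shading of self-report is unavoidable and openly disclosed. That is correct, and no change in form handling would remove it. It does not justify adding a second, avoidable source.

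Three stronger readings are tempting but not supported:

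- **Every effect favours the intervention.** TCs are trained to detect risk behaviours, and a trusting relationship could equally raise disclosure of alcohol and tobacco use.
- **TCs will coach towards individual items after seeing the answers.** Goals related to empowerment are part of the programme itself, and a TC could work on the scale's content without seeing anyone's form.
- **The false-positive rate of the primary test is 8% to 19%.** That range comes entirely from an assumed shift, and any real shift could come largely from unblinded self-report.

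**Conclusion.** The point holds as an avoidable bias route. The plan lets an unblinded deliverer of the programme enter and view data without a stated limit, and its safeguard covers only design and analysis.

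The exposure is clearest for the file-dependent knowledge items and the composite that uses knowledge. For GYPES and the other self-reported outcomes it is indirect, of unknown size and direction, and inseparable from the effect of unblinded self-report. A reader might infer that the primary comparison is compromised; the article does not show that.

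The conclusion assumes that the Data management wording means what it says, namely that TC access is not restricted elsewhere. It is a cheap improvement worth making, and the sample size and analysis are unaffected.

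**What to change.** Amend the Data management section as follows:

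- Restrict TC logins to recruitment, randomisation and process forms.
- Have outcome questionnaires from both randomised arms returned under code to existing staff who do not deliver the programme to those patients, and entered by them. This can be a DCO, the project coordinator or the other RCT centre.
- Score file-dependent knowledge items from a coded extract of the medical file that does not show the allocation.
- Tell participants in both randomised arms that their coordinator will not see their answers.

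The Blinding section and the limitations paragraph should then name this separation alongside the exclusion from analysis. If an operating procedure already provides it, citing that procedure and correcting Data management is enough.

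The cost is some transfer of data-entry work and the preparation of coded file extracts. The article reports that recruitment was under way at submission and that data collection was expected to run to December 2019, so the change could still cover later assessments, including the final one. Knowledge forms already scored could be re-scored in the same way.

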### Statistical analyses plan

The primary analyses will be performed following the intention-to-treat principle which helps to avoid biases in the comparisons between groups. The primary end point (level of empowerment) will be analysed using Fisher’s non-parametric permutation test unadjusted between the two groups. Complementary between-group analyses will be made using analysis of covariance adjusted for baseline variables that differ significantly between groups and for each centre.

All analyses will be predefined in a comprehensive statistical analysis plan before data lock. The level of significance will be at p≤0.05. Two-sided tests will be used.

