### Sample size estimation

Sample size calculation is based on the primary outcome of patient empowerment. The target is an improved patient empowerment score of 5.25 points on a scale from 15 to 75 (ie, 0.5 SD). For two-sided tests with α=0.05 and power=80%, 63 patients are needed in each arm of the RCT. In order to compensate for a potential 10% dropout rate, we will recruit 70 patients in each arm of the RCT. An additional 70 patients will be recruited in the centres of the control group. Among the four centres, a total of 210 patients will be enrolled (see figure 1).

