### Randomisation

Using a web-based system, a stratified block randomisation with a random variable block size will assign patients of the RCT centres to the intervention group or the comparison group (1:1).^21^ Block randomisation ensures that the TCs in the two centres have a relatively continuous exposure to the intervention over time, which allows them to keep their skills up to date and to ensure the fidelity of the intervention. The fact that the block sizes vary randomly minimises the possibility that the TCs could predict group assignments.

Stratification is made by centre and disease complexity. The stratification for centre ensures that the two centres have an equal number of intervention patients. Stratification by disease complexity (mild; moderate; complex)^22^ is important to avoid over-representation of those people with, for example, complex CHD in one or the other group due to failing randomisation.

Overall, this approach decreases the within-centres variability and reduces the risk for bias and confounding.^21^ The TCs are responsible for accessing the randomisation system in order to determine patient allocation.

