### Follow-up period and data collection

During the 2-year follow-up period, outcome measurements are assessed on three different occasions: T0, baseline when the participants are 16 years old; T1, midterm when the participants are 17 years; and T2, final data collection when the participants have been transferred to adult care and are ∼18.5–19 years old (see figure 1).

Participants from the intervention group will be mailed the set of questionnaires 1 month before the outpatient clinic visit. If the questionnaires have not been received by the time of the visit, they will have the opportunity to complete them while waiting for their appointment. Patients from the control and comparison groups may not have a scheduled outpatient visit. Therefore, data collection in these groups is completely undertaken by post when the participants are 16 (T0), 17 (T1) and 18.5 years old (T2).

To minimise non-response in the comparison and control groups, a modified Dillman procedure will be used.^26^ Two weeks after the documents are sent, non-responders will receive a first personalised reminder in the form of a text message. If after 4 weeks the questionnaires have not been received, a reminder letter and a new set of questionnaires is sent. After 6 weeks, persistent non-responders are contacted by telephone and asked whether they received the questionnaires, if the mailing address is correct, if they want a new set of questionnaires and if they want to continue participating in the study. After 8 weeks, a last reminder is sent to those who agree to participate in the study during the telephone call.

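### The primary test leaves out baseline GYPES and the stratification factors, and the complementary ANCOVA does not reliably bring them in: a loss of efficiency, not of validity

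*Protocol article*

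**What the plan says.** All references are to the Protocol article.

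- **Statistical analyses plan.** The level of empowerment is compared by Fisher's "non-parametric permutation test unadjusted between the two groups". A complementary ANCOVA follows. It adjusts for centre and for whichever baseline variables turn out to differ significantly between the groups. Full detail is deferred to an analysis plan to be completed before data lock.
- **Randomisation.** "Stratification is made by centre and disease complexity", with two RCT centres and three complexity levels, so six strata.
- **Follow-up period and data collection.** "outcome measurements are assessed on three different occasions: T0, baseline when the participants are 16 years old", then T1 and T2. The primary outcome scale is therefore available before the intervention.
- **Sample size estimation.** The target is a gain of 5.25 GYPES points, which the section equates with half an SD. On that basis it states: "For two-sided tests with α=0.05 and power=80%, 63 patients are needed in each arm of the RCT". Recruitment is set at 70 per arm to allow for 10% dropout. No credit is taken for a baseline correlation.

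**The concern.** The T0 score on the same 15-item scale is likely to be the strongest single predictor of the T2 score. A primary test that ignores it leaves removable variance in the comparison and carries part of any chance baseline difference into the estimate. The stratification factors were judged important enough to control in the allocation, yet they are not used in the primary test either.

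The complementary ANCOVA does not close the gap, because its selection rule looks at the wrong property. A covariate improves precision because it predicts the outcome, not because it happens to be imbalanced. Under sound randomisation, T0 GYPES will differ significantly at the 5% level in only about 1 trial in 20. Disease complexity is balanced by design through the stratification, so it will hardly ever qualify.

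At stake is the precision of the main result in a trial sized with little reserve beyond its 10% dropout allowance.

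**Working it through.** **Inputs from the protocol.** Difference 5.25 points = 0.5 SD, so SD = 5.25/0.5 = 10.5; two-sided α = 0.05; power 80%; 63 per arm analysed, 70 recruited; 1:1 allocation.

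**Assumed, not in the protocol.** The T0–T2 correlation r of GYPES, shown from 0.2 to 0.6; the share of outcome variance explained by the strata, R²; equal SDs in the two arms and at T0 and T2. The permutation test is represented by a two-sample t test.

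**Step 1: reproduce the plan's figure.** n per arm = 2(1.960 + 0.842)²/0.5² = 62.8, rounded up to 63. Power at 63 = Φ(0.5·√(63/2) − 1.960) = Φ(2.806 − 1.960) = 80.1%, or 79.5% by noncentral t. Dropout: 63/0.9 = 70. The plan's numbers hold, and they are those of an unadjusted comparison.

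**Step 2: adjust for T0 GYPES.** Residual SD = 10.5·√(1 − r²). Power is by noncentral t at 63 per arm. The detectable difference at 80% power is 2.80 × residual SD × √(2/63). The equivalent unadjusted n is 63/(1 − r²).

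| r (assumed) | Residual SD | Power | Detectable difference | Equivalent n per arm |
|---|---|---|---|---|
| none | 10.50 | 79.5% | 5.24 | 63 |
| 0.2 | 10.29 | 81.1% | 5.14 | 66 |
| 0.3 | 10.02 | 83.1% | 5.00 | 69 |
| 0.4 | 9.62 | 85.9% | 4.80 | 75 |
| 0.5 | 9.09 | 89.5% | 4.54 | 84 |
| 0.6 | 8.40 | 93.6% | 4.19 | 98 |

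Spending three more degrees of freedom on centre and complexity leaves these powers unchanged to three decimals.

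**Step 3: strata alone.** With residual SD = 10.5·√(1 − R²), power (normal approximation) goes from 80.1% to 80.9%, 82.1% or 84.1% for R² = 2%, 5% or 10%. The strata matter much less than T0 GYPES unless they are strongly prognostic.

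**Step 4: type I error.** If allocation is balanced within strata but the test ignores them, the actual two-sided level is about 2(1 − Φ(1.96/√(1 − R²))): 4.4% at R² = 5% and 3.9% at R² = 10%. The departure is in the conservative direction.

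**Step 5: simulation.** With 126 patients, six strata and 4,000 runs per setting, and strata explaining nothing, the unadjusted test had 79–80% power. ANCOVA on baseline and strata had 83%, 89% and 97% at r = 0.3, 0.5 and 0.7. With R² = 5%, the unadjusted test's type I error was 4.3–4.7% and ANCOVA's 4.9–5.1%.

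**Step 6: what the selection rule misses.** The SE of the baseline difference is 10.5·√(2/63) = 1.87 points, so a 5% baseline test flags only differences above 1.96 × 1.87 = 3.67 points. An unflagged imbalance of one SE shifts the unadjusted estimate by r × 1.87: 0.4 points at r = 0.2, 0.9 at 0.5 and 1.1 at 0.6, against a target of 5.25.

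**The case against.** The sample size and the primary test agree with each other: both are unadjusted, and the test delivers the power that was planned. An unadjusted permutation test is valid and needs few distributional assumptions. All of this stands. A reader might infer that the trial is underpowered, that its significance level is wrong, or that this choice is what would make a true 0.5 SD effect come out null. The protocol supports none of these. The chance of missing such an effect is essentially the 20% type II error accepted at design; adjustment would only make it smaller.

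The planned ANCOVA does always include centre, and it would take in a large baseline imbalance. That stands too. But it is complementary, and it fixes neither T0 GYPES nor complexity as a covariate.

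Two readings need care. First, the protocol does not describe the permutation scheme. Unrestricted permutation is the natural reading of an unadjusted test, but it is an inference, and the analysis plan may specify otherwise. The slight conservatism in step 4 depends on it. Second, the statistical section names neither a time point nor a change score. If change from T0 were analysed, baseline would be used. The stated hypothesis of a higher score favours the final value. Even for change, with SD 10.5·√(2(1 − r)), power (normal approximation) would be 66% at r = 0.3 and 80% at r = 0.5, against 84% and 90% for ANCOVA on the same approximation.

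Finally, the gain depends on an unknown correlation over an interval from age 16 to about 18.5–19. At r = 0.2 it is under 2 points.

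**Conclusion.** The point holds as a matter of efficiency. The primary test uses neither T0 GYPES (taking the end point as the final score) nor the stratification factors, and no planned analysis reliably adjusts for T0 GYPES and complexity. The sample size is correct. The test holds its level, with slight conservatism if the strata are prognostic and permutation is unrestricted.

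The avoidable loss at 63 per arm runs from about 2 percentage points of power at an assumed correlation of 0.2, through 10 at 0.5, to 14 at 0.6. Nearly all of it comes from T0 GYPES; the strata contribute about 2 points if they explain 5% of the variance. The direction is secure for any material positive correlation. The size is not, because the protocol reports no correlation.

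**What to change.** Make the primary analysis the between-arm difference in T2 GYPES with T0 GYPES, centre and disease complexity prespecified as covariates. This can be an ANCOVA. To keep the permutation approach, use the baseline-adjusted difference as the test statistic and permute within centre-by-complexity strata. Replace the rule that selects covariates by baseline significance with this fixed list, and keep the unadjusted permutation test as a sensitivity analysis.

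The cost is wording in the protocol and analysis plan. T0 GYPES is already collected, and centre and complexity are already needed for randomisation, so no extra patients or measurements are required. The article reports the trial as still recruiting, with analyses to be predefined before data lock, so the change can be made before the outcome data are examined.

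### The supporting ANCOVA chooses covariates by baseline significance tests, so in the randomised comparison it adjusts for chance differences and almost never for baseline GYPES or disease complexity

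*Protocol article*

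**What the plan says.** The Statistical analyses plan section tests the primary endpoint with "Fisher’s non-parametric permutation test unadjusted between the two groups". It then adds, as a complementary between-group analysis, an "analysis of covariance adjusted for baseline variables that differ significantly between groups and for each centre". Centre is therefore the only covariate known in advance. The threshold for a significant difference is the general one: "The level of significance will be at p≤0.05", and "Two-sided tests will be used".

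The Randomisation section allocates 1:1 within the two RCT centres, in blocks of randomly varying size. Besides centre, it uses a second factor: "Stratification by disease complexity (mild; moderate; complex". The Follow-up period and data collection section has outcomes measured at T0, so a baseline GYPES score is available. Nowhere does the protocol put baseline GYPES or disease complexity in the model unconditionally.

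**The concern.** A covariate belongs in an ANCOVA because it predicts the outcome or was used in the randomisation. The stated rule uses neither reason. It selects on the p-value of a between-arm comparison at baseline, and under sound randomisation that p-value reflects only chance.

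Three consequences follow:

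- The strongest candidate predictor, the T0 score of the same scale, is left out of nearly every realisation of the trial.
- One of the two stratification factors is left out by construction, because stratifying on it prevents the imbalance that would admit it.
- The model is unknown until the arms have been compared at baseline.

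At stake are the precision of the adjusted estimate and its usefulness as support for the primary result.

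**Working it through.** **Inputs from the protocol (Sample size estimation).** The target is an "improved patient empowerment score of 5.25 points on a scale from 15 to 75 (ie, 0.5 SD", so the SD is 5.25 / 0.5 = 10.5. The stated requirement is 63 per RCT arm, at 80% power and a two-sided 5% level, raised to 70 per arm to allow for 10% dropout.

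**Inputs not in the protocol (assumptions).** T0–T2 correlation r of GYPES, taken as 0.3 to 0.7; the number of baseline variables tested; block sizes of 2, 4 and 6.

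**1. The plan's own figure.** n per arm = 2 × (1.96 + 0.84)² / 0.5² ≈ 62.8, rounded up to 63; normal-approximation power at 63 is 80.1%. Allowing for 10% dropout, 63 / 0.9 = 70. Both stated figures reproduce.

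**2. How often each covariate is selected.** For an unstratified variable the chance is 5% by definition. In simulated stratified block allocation (2 centres × 3 complexity levels, N = 126 and 140, two complexity mixes, 4,000 trials each, 16,000 in all):

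- a baseline score such as GYPES was selected in 4.8% to 5.6% of trials;
- disease complexity was selected in none, and the smallest p-value seen was 0.55.

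**3. How often something is selected.** With k independent variables the chance of at least one is 1 − 0.95^k: 40% for k = 10, 54% for k = 15, 64% for k = 20. The Outcome measurements section lists ten background variables before any questionnaire score is counted.

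**4. Power available from baseline GYPES.** The residual SD is 10.5 × √(1 − r²). For r = 0.5 it is 9.09, the standard error of the difference is 9.09 × √(2/63) = 1.62, and 5.25 / 1.62 − 1.96 = 1.28, which gives 90.0% power. The third column below is this formula. The last two are simulated (6,000 trials per r), with the rule applied to baseline GYPES alone.

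| r | n per arm for 80% with ANCOVA | Power at 63: ANCOVA, formula | Power at 63: rule, simulated | Power at 63: unadjusted, simulated |
|---|---|---|---|---|
| 0.3 | 58 | 83.7% | 79.8% | 79.5% |
| 0.5 | 48 | 90.0% | 80.9% | 79.9% |
| 0.7 | 33 | 97.6% | 82.4% | 80.2% |

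**5. The rule with nine further baseline variables also tested** (6,000 trials per scenario). Power under the rule / unadjusted / ANCOVA on baseline GYPES:

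- r = 0.4: 79.3 / 79.5 / 85.8%
- r = 0.5: 80.5 / 80.2 / 89.8%
- r = 0.6: 80.0 / 79.5 / 93.5%

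Type I error at r = 0.5 was 4.1% under the rule and 5.0% with the covariate prespecified. A further run of 12,000 trials per scenario gave 5.0%, 4.2%, 3.8% and 4.0% under the rule at r = 0.3, 0.5, 0.6 and 0.7.

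**6. Imbalance the rule ignores.** The largest non-significant baseline gap at 63 per arm is 1.979 × 10.5 × √(2/63) = 3.7 points. Left unadjusted, it shifts the estimated difference by r × 3.7, which is 1.1, 1.9 and 2.6 points for r = 0.3, 0.5 and 0.7, against a target of 5.25.

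**The case against.** The strongest reply is that little depends on this analysis. The primary test is unadjusted, so its p-value, its validity and the sample size do not change, and the plan never claims that the ANCOVA adds power. Under the rule, power stays close to the planned 80% and the error rate is conservative, so no false-positive risk is shown. All of this stands and limits the point to the supporting analysis.

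The size of the lost gain rests on a correlation the protocol does not give, over follow-up from age 16 to about 18.5–19. That also stands. At r = 0.3 the gain is under 4 percentage points and the error rate is essentially nominal.

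The claim that baseline differences are chance holds only for intervention versus comparison. Against the intervention-naïve centres, differences need not be chance. Even within the RCT centres it presumes that T0 questionnaires are completed before allocation, which the article does not state. These are fair limits, but significance remains a poor selection rule for the non-randomised contrast too.

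Centre is always adjusted for, and nothing in the protocol shows that complexity predicts GYPES. Omitting complexity costs precision only if it does. The usual practice of keeping stratification factors in the model still argues for including it.

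Finally, a full SAP is promised before data lock and could fix the covariates. The protocol nevertheless states this rule outright, and a SAP that follows the protocol would inherit it.

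**Conclusion.** The concern holds for the randomised comparison. The covariate rule is stated, not merely left open, and it selects on the wrong criterion. Baseline GYPES enters in about 5% of trials and disease complexity in practically none. As written, the adjusted analysis performs almost the same as the unadjusted one: 80.5% against 80.2% power at an assumed r of 0.5, where a prespecified ANCOVA gives 89.8%. Over r = 0.3 to 0.7, prespecified adjustment reaches 83.7% to 97.6%. The type I error departs from 5% only on the conservative side, to about 4% for r of 0.5 and above.

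The selection rates do not depend on r; the power and error figures do, and those in step 5 also depend on the assumed number of baseline variables. The primary permutation test is unaffected. This should be corrected, but it does not threaten the main result.

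**What to change.** Remove the criterion based on significant baseline differences. For every ANCOVA between the intervention and comparison groups, fix the covariates as the T0 value of the outcome analysed (T0 GYPES for the primary endpoint), centre and disease complexity, whatever the baseline comparison shows. Describe the randomised arms at baseline without significance tests.

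For comparisons with the control centres, name a short list of prognostic covariates in advance. Centre cannot be one of them, because group and centre are fully confounded in that contrast.

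The cost is wording in the protocol and SAP. The T0 scores and the stratification factors are already collected, and the protocol's commitment to predefine all analyses before data lock leaves room for the change.
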